#### Mediterranean Diet Adherence Screener [32]

The MEDAS questionnaire was developed within the scope of the PREDIMED study. The evaluated English version was translated for the LIBRE-1 study and complemented by pictures of serving sizes (cf. CRF MED). The German version of the MEDAS will be validated within the scope of the pilot study. The MEDAS questionnaire is to be conducted at SE, V1, and V2 in both study arms.

#### Measurement of quality of life (EORTC QLQ-C30/-BR23) [33, 34]

In order to acquire health-related quality of life (HRQOL), a composed questionnaire, a 30-item core questionnaire (QLQ-C30), and a 23-item breast cancer module (QLQ-BR23) will be used before and after the intervention period [35]. The advantage of the QLQ-C30/-BR23 includes the present-day relevance and the previous validation for breast cancer (QLQ-BR23). Validation studies in European countries and the United States have been conducted in cross-cultural context [36, 37].

#### Measurement of optimism (life orientation test, ten items, LOT-R by Glaesmer et al. [38])

The LOT-R was developed to collect individual differences of generalized optimism versus pessimism in the form of a personality variable. It has been applied in various intervention studies, which, among other things, look at the consequences of dispositional optimism on behavior, emotion, and physical health. We hypothesize that regular physical activity and the implementation of healthy nutrition (IG) can lead to a more optimistic attitude to life.

#### Measurement of chronic stress [39]

The SSCS by trier inventory on chronic stress is a 12-item (short version) questionnaire, which measures five different aspects of chronic stress: lack of social recognition, pressure of business, social stress, chronic anxiety, and overstrain [39].

#### Measurement of attitudes and views on physical exercise and healthy eating (BKAE, 18 items)

One of the main intentions of the present LIBRE study is to investigate the practicability of the intervention program in the sense of good compliance of mutation carriers towards an exercise program and Mediterranean diet. In order to understand how different factors may influence compliance, measurements of subjective parameters are needed (such as attitudes towards a behavior, subjective norms, and perceived behavior control), which represent a necessary link between objective factors (age and other demographics, stage of disease, comorbid conditions, treatments, stress pressure, daily hassles, etc.) and intentions related to behavior as well behavior itself (doing sports and keeping a specific diet). According to the theory of planned behavior (see Fishbein and Ajzen [40]), the intentions related to behavior result from an interplay between attitudes towards a behavior, subjective norms, and perceived behavior control. The theory of Fishbein and Ajzen was applied in the last years in many studies which dealt with health psychology (e.g., surgery intentions, food adherence, and physical activity behavior among others) and represents one of the well-proven ways to investigate subjective mechanisms of compliance [41–44]. In the context of the Fishbein and Ajzen [40] model, the study may answer the following questions: (1) Which are the predictors of regular participation in the preventive measures (exercise, nutrition)? (2) To which degree are attitudes, subjective norms, or perceived behavior control towards a behavior relevant for the intention of behavior (i.e., to train regularly and to eat healthy) and for the de facto behavior shown?

### Study endpoints

The primary endpoint of the study is the number of randomized women who successfully complete the first 3 months of the intervention program and the monitoring/maintenance phase after 1 year. The study is considered feasible if at least 70% of the patients fulfill the criteria (see Table 4 for details).

**Table 4 Tab4:** Criteria for successful completion

Attendance of 70% of the planned lifestyle intervention events (training sessions and nutrition courses) within the first 3 months • Conduct of study visit after 1 year • No withdrawal of informed consent within 1 year • No new occurrence of any of the exclusion criteria during the first 3 months	

Secondary endpoints of the study include the measurements of quality of life (EORTC QLQ-C30-/BR23), stress coping (SSCS), optimism grade (LOT-R), body mass index (BMI), eating habits, nutrient and fat calorie intake (EPIC-FFQ), adherence to a Mediterranean diet (MEDAS), maximal oxygen intake (VO_2_ max), and physical activity (IPAQ). These measurements will be performed after 3, 6, and 12 months of intervention and compared to the baseline measurements at SE.

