**Methods:**

Therefore, we intend to enroll 60 BRCA1/2 mutation carriers in a pilot feasibility study (Lifestyle Intervention Study in Women with Hereditary Breast and Ovarian Cancer (LIBRE) pilot). This multi-center, prospective, controlled trial aims to randomize (1:1) participants into a (1) multi-factorial lifestyle intervention group (IG) versus (2) the control group with usual care (CG). The primary endpoint is feasibility and acceptance of a structured interdisciplinary lifestyle intervention program over 12 months (at least 70% of the patients to complete the 1-year intervention). Furthermore, the effects on physical fitness, BMI, quality of life, and stress coping capacity will be investigated.

During the first 3 months, women in the IG will receive structured, individualized and mainly supervised endurance training of ≥18 MET*h/week (MET = metabolic equivalent task) and personal nutritional counseling based on the Mediterranean diet. During the subsequent 9 months, the IG will receive monthly group training sessions and regular telephone contacts for motivation, whereas the CG will only receive usual care (one general counseling on healthy nutrition and benefits of regular physical activity on health status). At randomization and subsequent time points (3, 6, 12 months), cardiopulmonary fitness will be assessed by spiroergometry and nutritional and psychological status by validated questionnaires.

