*Physical activity*: The LIBRE training program is primarily an endurance-oriented training, which will be completed in the course of 1 year. After a mandatory introductory lecture on the theory behind the intervention training, the goal is to increase physical activity to ≥18 MET*h/week (MET = metabolic equivalent task). One MET is equivalent to resting energy expenditure, so multiple METs express exercise intensity that is performed over a certain time, e.g., hours per week. 18 MET*h/week is approximately equivalent to brisk walking (4.5 MET) for 4 h per week. This activity level has been correlated consistently with a reduction of morbidity and mortality in breast cancer patients [8, 21]. This goal should be achieved within the first 12 weeks and maintained throughout the whole study period. Each subject will receive an individual training plan, which will continuously be adapted according to her fitness status. The training plan is divided into two phases: the intensity of the initial phase, weeks 1–6, should be at least 50–60% of the peak oxygen consumption (VO_2_ peak), and the optimization phase, weeks 7–12, 60–75% of the VO_2_ peak. In the first 12 weeks of the intervention program, training will take place twice a week as supervised training and once a week as home-based training (HBT). Afterwards, supervised training units will only be carried out monthly, so that training in months 4–12 will be mainly HBT. Training will continue to take place with an intensity of at least 60–75% of the VO_2_ peak in accordance with the individual training plan.A record of compliance with the training intervention program as well as the achieved MET*h/week will be kept in the training diaries (questionnaire on physical activity, V0–V2). Participants should record their daily activities as well as intentional physical activity including intensity and duration of training. The training intensity levels will then be assessed by spiroergometry and outlined in the diary, which facilitates training control. Monthly supervised training units (as of V1) offer the opportunity to realign training intensity and discuss any problems with adherence to training. In addition, physical activity is to be recorded using questionnaires (International Physical Activity Questionnaire (IPAQ) [22, 23] from V0 to V2), motion sensors (accelerometer from SE to V2), and a physical fitness assessment by cardiopulmonary exercise testing by spiroergometry (VO_2_ peak) [24] at time points SE, V1, and V2.

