*Nutrition*: Within the framework of the LIBRE-1 study, the nutrition intervention is based on the principles of a Mediterranean dietary pattern (MD). Furthermore, obese patients (BMI ≥ 35 kg/m^2^) will be instructed to limit their energy (kcal) intake. Nutrition intervention in the IG consists of an intensive phase of 3 months in line with the intensive physical exercise program. During this phase, bi-weekly nutrition education group courses will be held by dietitians. They include a cooking class and guided tour of a supermarket. Afterwards, nutrition courses will be reduced to monthly intervals. The main objective of the nutrition intervention is to provide practical nutritional training, which should enable the subjects to achieve a long-term change in their eating habits, replacing it with the MD. Eating habits will be recorded using validated questionnaires (EPIC-Food Frequency Questionnaire (FFQ) and Mediterranean Diet Adherence Screener (MEDAS)) at the time points SE, V1, and V2. The questionnaires are described below in the “Measurements” section.
*Psychological support*: Explicit psychological support is not planned. Psychological support of the IG will comprise solely of an explanation of the psychological data survey questionnaires given to the study participants. The participants will be informed that the objective of the lifestyle study is, among others, that the lifestyle change including regular physical activity and healthy eating should lead to an improvement in general life quality, stress reduction, and a more optimistic outlook on life. In order to verify this, the participants will receive questionnaires (Screening Scale for Chronic Stress (SSCS), Life of Orientation Test-Revised (LOT-R), European Organisation for Research and Treatment of Cancer (EORTC) Quality of Life Questionnaire Core 30 and Breast Cancer Module 23 (QLQ-C30/-BR23), and Assessment of physical activity and nutrition (BKAE)) at several time points (SE, V0, V1, V2). Advice on the psycho-oncological aspects of the LIBRE study will be given during the introduction lecture at the beginning of the study. The psychological advice given to the study participants will serve to inform the subjects of the significance and improvement of psycho-social lifestyles for the prevention of breast and ovarian cancer, as well as to promote compliance and recognize possible psychological impediments for participation in the study.

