## Discussion

To the best of our knowledge, the LIBRE-1 study is the first prospective randomized lifestyle intervention trial in BRCA mutation carriers worldwide. Since the patients in the intervention arm will be given a strict and intensely structured intervention program, the purpose first is to assess the feasibility of the study design in a multicenter setting including 60 female mutation carriers. We are aware that the study protocol is time-consuming and demanding for the patients including regular exercise and changes in nutritional habits but believe it necessary to cover/investigate all relevant factors. Especially, during the first study visit, the questionnaires amount to a large contribution for the participants. However, the questionnaires can be answered during the waiting time between the examinations, e.g., spiroergometry, ECG, and body composition, lasting approximately half a day. In order to meet a high compliance rate, all participants will be informed beforehand about the time necessary for study examinations. For the time spent for examinations, patients will also receive a small financial reimbursement.

The Mediterranean diet though is widely accepted as a healthy diet in Germany. In addition, randomized controlled intervention studies have revealed that it is effective in the primary prevention of cardiovascular diseases [45], in improving diabetes [46] and cognitive function [47], and recently also in the primary prevention of invasive breast cancer [48].

Once compliance and acceptance of the study protocol have been proven (LIBRE-1), we will proceed with a larger cohort of mutation carriers with the intention to investigate whether the improvement of physical fitness, body weight, quality of life, and stress coping capacity leads to a reduction of breast cancer risk, progression of disease, and even mortality. On the basis of the LIBRE-1 results, it will be possible to outline a lifestyle program with high adherence even over 12 months of intervention (LIBRE trial). The current feasibility study will also reveal barriers to and constraints of the intervention, which will then have to be modified for the larger clinical trial.

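### Table 4 sets no adherence requirement after month 3, and its pooled attendance rule can probably be met without attending any nutrition course

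*Protocol article*

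**What the plan says.** The abstract gives the primary endpoint as "feasibility and acceptance of a structured interdisciplinary lifestyle intervention program over 12 months" and ties success to at least 70% of patients completing the year. Under Trial design, the aim is to evaluate adherence to a 1-year exercise programme combined with a Mediterranean diet. Under Study endpoints, a success must complete the first 3 months and also "the monitoring/maintenance phase after 1 year".

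Table 4 turns this into four criteria:

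- "Attendance of 70% of the planned lifestyle intervention events (training sessions and nutrition courses) within the first 3 months"
- the study visit after 1 year is held
- "No withdrawal of informed consent within 1 year"
- "No new occurrence of any of the exclusion criteria during the first 3 months"

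The section Statistical analysis and randomization confirms that Table 4 decides the primary endpoint.

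Under Intervention group, supervised training runs twice a week for 12 weeks, with one home session a week. After that, supervised units are monthly and training is mainly home-based. On the activity goal of at least 18 MET*h/week, the article says: "This goal should be achieved within the first 12 weeks and maintained throughout the whole study period". For nutrition in the first 3 months, "bi-weekly nutrition education group courses will be held by dietitians", and courses then become monthly.

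**The concern.** Months 4 to 12 are the part of the programme where supervision drops from twice weekly to monthly and the women are largely left to train on their own. Whether they keep going is the uncertain part of a 12-month feasibility question. Table 4 gives that period no weight beyond retention.

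Within months 1 to 3, one percentage covers two kinds of event that occur in very different numbers. The more frequent kind may be able to carry the threshold alone, although diet is one of the two components named in the aim.

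The result opens or closes the way to the larger trial. The Discussion says that the team will proceed once compliance and acceptance are shown, and that from the LIBRE-1 results "it will be possible to outline a lifestyle program with high adherence even over 12 months of intervention". A verdict of feasible under Table 4 could be taken as 12-month adherence to both components when the criterion does not test that.

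**Working it through.** The article gives no event count, so there is no figure of its own to reproduce. The counts below come from its schedule.

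**Step 1: what each Table 4 criterion covers**

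| Criterion | Period | What it measures |
|---|---|---|
| 70% attendance | months 1–3 | participation |
| No new exclusion criterion | months 1–3 | continued eligibility |
| 1-year visit held | month 12 | retention |
| Consent not withdrawn | to month 12 | retention |

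No row covers the monthly training units, the monthly nutrition courses, home training or the MET*h/week goal in months 4–12. Attending none of these sessions and stopping home training is compatible with meeting all four rows. This step needs no assumption about event counts.

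**Step 2: can nutrition be skipped under the pooled rule?**

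Inputs:

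- Supervised training: T = 2 per week × 12 weeks = 24.
- Nutrition courses, if held every two weeks: N = 12 / 2 = 6.

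Attendances needed = 0.70 × (T + N), rounded up. All nutrition can be skipped if T / (T + N) is at least 0.70.

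Base case: 0.70 × 30 = 21. Full training with no nutrition gives 24/30 = 80%. A woman could miss 3 training sessions as well and still reach 21/30 = 70%.

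| Reading | T | N | Needed | All training, no nutrition | Rule met? |
|---|---|---|---|---|---|
| Base case | 24 | 6 | 21 | 80.0% | yes |
| 7 courses | 24 | 7 | 22 | 77.4% | yes |
| Cooking class and supermarket tour counted as extra | 24 | 8 | 23 | 75.0% | yes |
| 13 weeks | 26 | 7 | 24 | 78.8% | yes |
| Home sessions counted | 36 | 6 | 30 | 85.7% | yes |
| Courses twice a week | 24 | 24 | 34 | 50.0% | no |
| Courses twice a week, home sessions counted | 36 | 24 | 42 | 60.0% | no |

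With 24 training sessions, all nutrition can be skipped for up to 10 courses (24/34 = 70.6%), but not for 11 (24/35 = 68.6%).

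**Step 3: approximate share of the year's group events**

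Assume 9 monthly training units and 9 monthly courses in months 4–12, held as separate events. The year then has 30 + 18 = 48 scheduled group events, and 21/48 = 44% is enough. Home training, the main mode in that period, is not in this count, so the figure is only a rough guide.

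**The case against.** Several objections have force.

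- *Later adherence is measured.* Diaries record training compliance and achieved MET*h/week from V0 to V2. Table 1 schedules IPAQ and accelerometry at 3, 6, 9 and 12 months, and the nutrition questionnaires at 6 and 9 months in the intervention arm. MEDAS, IPAQ and VO2 max are secondary endpoints. A reader might infer that the trial will learn nothing about adherence after month 3, and the documents do not support that. The objection does not rescue the primary endpoint, because none of these data enters Table 4.
- *The nutrition point depends on a reading.* It needs the 70% to apply to the combined set, which is the plain wording, and bi-weekly to mean every two weeks. The second is more plausible beside twice-weekly training, but it is not stated. A reader might take it as established that every course can be skipped; that is conditional. Nor does anything in the article suggest that high training attendance with no nutrition attendance would be common.
- *The Discussion speaks of LIBRE-1 results as a whole.* It does not say that Table 4 alone will show 12-month adherence, and it expects the programme to be modified. That is fair. The contradiction rests on the endpoint sentence, the abstract and the aim.
- *A descriptive pilot may choose a lenient criterion, and Table 4 is printed in full.* True, but the endpoint sentence and the conclusion must then describe what is counted.

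It is also tempting to convert the attendance threshold into a share of the MET*h/week goal. The article gives no session length, and home training contributes too, so no such figure can be supported.

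**Conclusion.** The point about months 4–12 holds without assumptions. As written, the primary endpoint measures 3-month attendance plus 12-month retention, while the article calls it completion of a 1-year programme including the maintenance phase.

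The pooling point holds on the plain wording of the rule and on a two-week course interval. It holds in all five such variants tried and fails in both twice-a-week variants. The 44% figure is an approximate share of scheduled group events and rests on an assumed 9 + 9 later events.

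The consequence is limited to what a verdict of feasible can support. It would not by itself show adherence over 12 months, nor adherence to both components.

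**What to change.** Either of two changes would bring the endpoint and its description into line.

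(a) Extend Table 4. Add an adherence criterion for months 4–12 that uses attendance at the monthly sessions together with the training diary and its MET*h/week record. Session attendance alone would not show whether home training continued. Set a minimum for each component in months 1–3, and state the planned number of each type of event, which also settles what bi-weekly means. The levels are for the trial team to choose. Purely as an illustration, applying 70% to each component in the base case would require 17 of 24 training sessions (0.70 × 24 = 16.8) and 5 of 6 courses (0.70 × 6 = 4.2).

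(b) Keep Table 4, but restate the endpoint and the feasibility conclusion as 3-month attendance plus 12-month retention. Report as named feasibility outcomes the attendance by component, the attendance in months 4–12, and the proportion meeting the protocol's own MET*h/week goal.

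The cost is mainly wording. The diary is already planned, and attendance has to be recorded for months 1–3 anyway, so continuing the lists adds little. Under (a), the completion rate may be less favourable.

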**Discussion:**

This pilot study will investigate the optimal strategy to improve physical fitness, nutritional habits, and psychological factors in women at high risk for developing breast or ovarian cancer. The results of this pilot feasibility study will be the basis for a larger prospective randomized trial including clinical events (LIBRE).

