### Participants

The goal is to recruit a minimum of 60 patients for the feasibility study. Recruitment and study conduct take place at three centers in three different regions in Germany (Munich, Kiel, and Cologne). Patients will be recruited from the German Consortium Hereditary Breast and Ovarian Cancer (GC-HBOC), a national registry for BRCA1 and 2 carriers. BRCA1- or 2-positive participants have been included in this surveillance program before and are contacted on a regular basis regarding clinical events. They have previously received genetic analysis mainly because of an amplified family history for breast cancer. They have received additional counseling before and are aware of their cancer lifetime risks. Table 2 details the study’s inclusion and exclusion criteria. Contacting the carriers for potential inclusion in the LIBRE-1 study will be done by the local study centers which are familiar with the patient history. Patients will either be contacted by telephone or during their regular visits to the hospital. Information regarding the LIBRE-1 trial will be given in person by physicians involved in the GC-HBOC program and previously instructed regarding the LIBRE-1 study. If patients agree to participate in the trial, they will have to sign consent forms and, if eligible, will be enrolled into the trial.

**Table 2 Tab2:** Study population: inclusion and exclusion criteria

Inclusion criteria (all criteria must apply): • Women with a pathogenic BRCA1 or BRCA2 germline mutation • Age between 18 and 69 years • Written informed consent	
Exclusion criteria: • Metastatic tumor disease • Expectancy of life <3 years • Limited cardiovascular and lung diseases (instable CHC, heart failure stage IV, COPD GOLD IV, maximal blood pressure at rest >160/100 mmHg) • Significant orthopedic problems, not allowing exercise • Serious diseases, not allowing a participation in group interventions (e.g., psychiatric or internal ailment) • Karnofsky status scale <60% • Women with VO_2_ max > 150% of general population • Women with an exercise capacity <50 W • Food allergies not allowing consumption of a Mediterranean dietary pattern • Vegans • BMI < 15 kg/m^2^ • Pregnancy • Insufficient knowledge of the German language • Current participation in other lifestyle intervention trials	

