#### Exercise testing/spiroergometry

Spiroergometry is an objective and well-known examination assessing cardiopulmonary exercise capacity. As the maximal oxygen uptake (VO_2_ max) and the aerobic and anaerobic respiratory capacity will be measured, the results enable a precise statement about the maximum cardiopulmonary capacity as well as aerobic and anaerobic capacity. The following target parameters (VO_2_ peak and O_2_ at ventilator anaerobic threshold (VAT)) [24] provide information about the fitness level at visits SE, V1, and V2.

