### Statistical analysis and randomization

The sample size for the feasibility study is to be at least 60 women. For this study, the sample size was not determined based on statistical assumptions and tests, but on practical grounds that each center should recruit 20 participants. Primary and secondary endpoints will be analyzed descriptively. The primary endpoint will be determined according to the criteria shown in Table 4. Secondary endpoints will be described using absolute or relative frequencies, means with standard deviations, or medians with inter-quartile ranges as appropriate, for each of the study arms at the different time points. Measurements at months 3, 6, and 12 will be compared and tested against the baseline values using either parametric or non-parametric tests as appropriate. Randomization is to take place using envelopes, which will be deposited at the study center before the study begins. The group allocation (randomization) will be done centrally, using randomly permuted blocks of length 2–6. The randomization ratio is to be 1:1. We will use participating center and previous breast cancer as stratification factors. Each center will receive consecutively numbered, opaque envelopes, unique to them, split into two sets (one for previously diseased and one for healthy participants), containing the results. For each new participant, the principal investigator in the center will choose and open the first envelope from the diseased or healthy batch accordingly. As the study is not blinded, the allocation result will be concealed neither from participants nor from the principle investigators.

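### Table 4's blanket exclusion clause would score a woman as a primary-endpoint failure if her VO2 max rises above 150% of norm by month 3; probably few women are affected, but the error can only lower the completion rate

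*Protocol article*

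**What the plan says.** The primary endpoint is the number of randomized women who complete the 3-month programme and the maintenance phase to 1 year (Study endpoints). The section on statistical analysis and randomization makes Table 4 decisive: "The primary endpoint will be determined according to the criteria shown in Table 4". The decision rule is: "The study is considered feasible if at least 70% of the patients fulfill the criteria".

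Table 4 has four conditions: 70% attendance at planned events in the first 3 months, the 1-year visit, no withdrawal of consent, and "No new occurrence of any of the exclusion criteria during the first 3 months". The last condition carries no exception.

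Table 2 (Participants) lists 14 exclusion criteria, one of which is "Women with VO_2_ max > 150% of general population".

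Training in the same window steps up to "the optimization phase, weeks 7–12, 60–75% of the VO_2_ peak". The abstract gives fitness as a target: "This pilot study will investigate the optimal strategy to improve physical fitness, nutritional habits, and psychological factors". The spiroergometry measures "provide information about the fitness level at visits SE, V1, and V2", and V1 is the 3-month visit. VO2 max is also a secondary endpoint, tested against baseline.

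**The concern.** Most of the exclusion criteria, such as metastatic disease, orthopedic problems, serious illness or pregnancy, plausibly bear on whether a woman can carry on with the programme. Counting their new occurrence as non-completion is defensible. The VO2 max ceiling is different in kind. It filters out very fit women at entry and says nothing about adherence, acceptance or ability to continue, which is what the trial sets out to measure.

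The word any brings this ceiling into the success definition. A gain in fitness can then turn an otherwise complete record into a failure on the primary endpoint while improving the secondary endpoint. No woman can become a success through this route, so the error has one direction. The completion rate is the stated basis for going on to the larger LIBRE trial, so a systematic downward error in it matters even if it is small.

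**Working it through.** **1. The logical check.** Table 4 determines the primary endpoint. Table 4 fails a woman on any newly met exclusion criterion in months 0–3. Table 2 includes VO2 max > 150%. Take a woman who enters at or below 150%, attends at least 70% of events, keeps her consent, attends the 1-year visit and measures above 150% at V1. She meets the other three conditions and fails this one. No sentence in the article prevents that result.

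**2. The decision rule.** Three centers × 20 = 60 women, which reproduces the stated sample size; 1:1 allocation gives 30 per arm. The 70% rule means 0.70 × 30 = 21 women if it is applied to the intervention arm, or 0.70 × 60 = 42 if applied to all. One failure at the threshold gives 20/30 = 66.7% or 41/60 = 68.3%, both below 70%.

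**3. Who could cross.** With relative gain g, a woman crosses if her entry value exceeds L = 150/(1+g):
- g = 5%: 142.9% of norm
- g = 10%: 136.4%
- g = 15%: 130.4%
- g = 20%: 125.0%

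**4. How many might cross (assumptions, not in the article).** The article gives neither a fitness distribution nor an expected gain. Assume entry values normal with mean m and SD s, cut at 150%, and the same gain for every woman. The share crossing is

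[Φ((150−m)/s) − Φ((L−m)/s)] / Φ((150−m)/s).

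For m = 100, s = 20, g = 10%: (0.9938 − 0.9655)/0.9938 ≈ 0.0285, or 0.85 of 30 women. Expected number of 30 in other cases:

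| Mean, SD | g = 5% | g = 10% | g = 20% |
|---|---|---|---|
| 90, 15 | 0.005 | 0.03 | 0.29 |
| 100, 15 | 0.05 | 0.22 | 1.42 |
| 100, 20 | 0.30 | 0.85 | 3.00 |
| 110, 25 | 1.26 | 2.89 | 6.97 |
| 115, 25 | 1.69 | 3.77 | 8.61 |

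Only women who otherwise meet Table 4 can be misclassified. At 70–80% completion, and taking crossing as independent of the other criteria, 0.85 becomes 0.60–0.68 and the extreme 8.61 becomes 6.0–6.9.

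**5. Effect on the decision.** The binomial probability of exactly 21 of 30 is 0.157, 0.130 and 0.068 at true completion rates of 70, 75 and 80%. For illustration, suppose 2% of otherwise successful women are lost through this clause at a true rate of 75%. The effective rate is 0.75 × 0.98 = 0.735. The chance of reaching the threshold falls from 0.80 to 0.75 with 30 women. With 60 it falls from 0.85 to 0.78, but that overstates the effect, because it applies the same loss to the untrained control arm.

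**The case against.** The strongest case against is that this is loose drafting in one clause of a descriptively analysed pilot, where the authors may have meant medical events only. Four parts of it stand.

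- **Frequency is unknown.** The trial admits women up to age 69 and women with previous breast cancer, so below-average entry fitness is plausible and the expected number may be well under one. The article's Discussion expects selection of motivated women, which would push the other way, but it gives no figure.
- **Timing is not airtight.** The clause covers the first 3 months, and V1 falls at their end. No other spiroergometry is scheduled between entry and 12 months. The natural reading includes V1, but the text does not settle it.
- **Other criteria in the clause are reasonable.** The fault lies in the unqualified any, not in the whole condition.
- **The ceiling is not the only entry filter.** Participation in another lifestyle trial raises the same question.

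A reader might infer that the clause penalises the most adherent women. The article does not support that: by step 3, crossing depends heavily on entering well above average fitness, and nothing links entry fitness to adherence.

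The objection does not remove the conflict. The article itself fixes the criterion, so a later plan that exempted VO2 max would contradict Table 4, not fill a gap in it.

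**Conclusion.** The definition is wrong as written. Applied literally, it can fail a woman on the primary endpoint for a fitness gain the programme seeks, and it can only lower the completion rate.

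The number affected cannot be derived from the article and is probably small. The range from near 0 to several of 30 rests entirely on the assumed entry distribution and gain. It is smaller again among women who otherwise meet Table 4.

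A reader might conclude that the go/no-go decision is materially biased. The article does not support that. One such woman reverses the decision only if the count without this clause would have been exactly at the threshold, V1 is counted inside the window, and the clause is applied to the letter. Severity is minor to moderate: the likely effect is modest, but the conflict is clear and cheap to remove.

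**What to change.** In Table 4, exempt the criterion of VO2 max above 150% of the general population from the condition on newly occurring exclusion criteria. In the same line, state whether other pure entry filters, such as joining another lifestyle trial, count as failure once a woman is enrolled.

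In the results, report women who fail on this condition alone separately from those who fail on attendance, withdrawal or the 1-year visit.

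The cost is one line in Table 4 and one extra row in the results table. No new data are needed, and the sample size, the eligibility criteria at entry and the 70% rule stay as they are.
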